**For female participants only**					
ABI-R [36]	Revised Abusive Behaviour Inventory. To assess the effect of the intervention on measures of experience of DVA, health and wellbeing of female (ex)partners				
CHU-9D [56]	Proxy version: Child Health Utility Index – 9 Dimension. A health-related quality of life measure for one child (the child with the first birthday in the calendar year), which can be used to calculate QALYs (Quality Adjusted Life Years)				
Children’s resource use	Health care use and missed days at school for one child aged 5–18 years (the child whose birthday was first in the calendar year).				

#### Secondary outcomes: Police data

We will collect police-recorded DVA incidents and crimes perpetrated by our male participants. We will collect data for the 12-month period prior to randomisation and 12 months post-randomisation (see Supplementary Information: RESPONSE TO COVID-19 PANDEMIC). We will request for each male participant the following: (a) a count of the number of police incidents/crimes flagged as DVA; (b) the date(s) of the incident(s)/crimes; (c) the police case outcome for each incident/crime (for example, *No Further Action*, *Charge*, *Domestic Incident only*); (d) a count of the number of entries on the Log of Enquiries for each of these incidents; (e) risk scores/ratings for each of these incidents where available and whether referred to Multi Agency Risk Assessment Conference (MARAC).

Pre- and post-randomisation police DVA incident data are another measure of participant behaviour change. The risk scores/ratings and the police case outcome will also give an indication of the severity and nature of the abuse. Finally, the police data give an external source of data distinct from the participants’ self-reports of abuse.

#### Process evaluation

Programme process will be monitored to assess delivery of the intervention across the different service providers and to compare with the intended intervention model. Group attendance data and reasons for absence will be collected to help assess the intervention *dose* that each man received and their levels of engagement. Session notes from the group facilitators will be used in conjunction with video recordings of weekly sessions (which are part of normal DAPP delivery) and observations to ascertain the fidelity to the model (for example, were session objectives achieved, adherence to programme principles, adherence to or deviation from the manual). Numbers of one-to-one DAPP coordinator contact with men and the broad purpose for these individual sessions will be collected. The frequency and type of contact (face-to-face, online, telephone) and main purpose of contact between the WSW and (ex)partners will also be collected.

#### Nested qualitative study

A qualitative study will be undertaken using semi-structured interviews with study participants to elicit their perspectives on key aspects of the intervention and study experience. We will, for example, seek to gain feedback on experiences of the intervention (male and female intervention participants) and a better understanding of any changes in abusive behaviours during the study period (all male and female participants). Using topic guides, likely questions for male and female control participants will include whether they felt they were being monitored in any way while being part of the trial. We will interview some professional referrers and staff in different provider roles (DAPP coordinator, group facilitator, managers) regarding their experiences of referring to or delivering the group intervention and of supporting (ex)partners. Data will be collected on the context of the intervention at each centre partly through interviews and a few observations of the group sessions at each centre. Contextual data will also be captured through ongoing gathering of external information such as information about alternative DAPP providers in each centre and dates the COVID-19 lockdown rules changed (different for England and Wales). These qualitative data will help articulate likely challenges in future implementation (if the intervention proves cost-effective) and help to interpret the quantitative results. Interviews will be recorded on an encrypted device and stored securely on university servers. They will be transcribed and anonymised, and coded thematically by members of the research team, with some interviews being coded by more than one researcher to ensure inter-rater reliability.

#### Economic evaluation measures

All resource use in relation to participants’ own use of health services (secondary, community and mental health based), medications, personal social services (e.g. drug and alcohol team), voluntary sector services, criminal justice and legal services will be collected for the 12 months following randomisation by means of self-reported questionnaire, and in the case of police incidents, the police-recorded data. These questionnaires will also collect information on out-of-pocket expenses, e.g. personal counselling, complementary therapy, relocation costs and childcare costs, in addition to time off work.

Additionally, the use of health services and time off school by any children who primarily live with the supporting (ex)partner is being collected through their respective questionnaire. Three outcomes for the economic evaluation: EQ-5D-5L [38], SF-12 [39] and ICECAP-A [40] are being collected for all participants; additionally, the proxy version of the CHU-9D [56] is being collected in the supporting (ex)partner questionnaire for the child whose birthday is first in the calendar year. The NICE recommended mapping function [57] will be used to calculate quality-adjusted life years (QALYs) in relation to the EQ-5D-5L. The SF-6D and its preference weights [58] will be used to calculate QALYs in relation to the SF-12. A published value set [59] will be used to calculate QALYs in relation to the CHU-9D.

The resource use and costs incurred in relation to the intervention: the group intervention (both main and RPG) as well as the individual sessions for men and support from the WSW for the (ex)partners will be obtained from the budget breakdown.

### Participant timeline {13}

A potential participant will have an initial telephone discussion with a researcher for eligibility screening and an explanation of the study. If eligible and interested, a participant information sheet will be sent electronically or by post according to preference. If the potential participant is happy to proceed, a date and time will be agreed for a joint recruitment and assessment meeting with the potential participant, researcher and local DAPP coordinator. At the recruitment meeting, the researcher checks the potential participant’s ID, understanding of the study and re-checks eligibility, while the DAPP coordinator assesses suitability to potentially join a perpetrator group programme. If there are any concerns about lack of understanding, motivation or risk, the meeting may be paused, and another appointment made if more investigations are needed, or the potential participant requires more time to think. The process may be stopped altogether if it is felt inappropriate to recruit the potential participant or if he decides he no longer wishes to proceed. If the participant is happy to proceed, signed informed consent is taken by the researcher, and contact details of the participant’s (ex)partner[s] (up to two (ex)partners per male participant), general practice and any other agencies (mental health, substance misuse or social workers) will be requested.

The male participant will either complete the baseline questionnaire before the assessment (if online) or in the presence of the researcher if face-to-face (see also Supplementary Information: RESPONSE TO COVID-19 PANDEMIC). Once recruitment and baseline assessments are completed, the participant is randomised and immediately informed of the results and the next steps in the research (Table 4).

**Table 4 Tab4:**
[figure not shown]
Schedule of enrolment, interventions and assessments

*DAPP* Domestic abuse perpetrator programme, *RPG* Relapse prevention group, *ABI-29* Abusive behaviour Inventory [29]

The female (ex)partners of perpetrator participants will be contacted about the study before the male assessment meeting where possible and the study explained to them. After the assessment, the (ex)partners will be informed of his participation and (for safety purposes) allocation in the study and invited to consider taking part in the study themselves. If potential study participation is agreed, a meeting with the researcher will be arranged at a safe and mutually convenient location or online or by phone. At this meeting, eligibility will be checked, informed consent sought and baseline questionnaire completed. (Ex)partners unable to meet in person may still participate in the study by returning electronic or postal consent and questionnaires (see Supplementary Information: RESPONSE TO COVID-19 PANDEMIC).

For (ex)partners of men allocated to the intervention arm, the associated women’s safety worker will contact the partner to offer support. This support will be offered whether or not the woman consents to participate in the study. (Ex)partners of men allocated to the control arm will be signposted to local and national DVA support services.

The flow of male participants and recruited (ex)partners through the trial is summarised in Fig. 2 and in Table 4.

**Fig. 2 Fig2:**
[figure not shown]
Participant timeline

### Sample size {14}

In all power calculations, we have assumed a 2:1 allocation ratio (intervention: control) and applied a two-sided significance level of 5%. Our initial assumption was that a total of 219 participants would be available for analysis which, after inflation to allow for 40% attrition gives a total recruitment target of 366 participants (244 intervention and 122 control).

The (primary) power calculation used the power command in Stata 15.1, which yielded 79% power for an effect size of 0.4 standard deviations (0.4SD). While there is no established minimal clinically important difference on the ABI-29 scale, baseline data from male perpetrators in a group support study in the US using the ABI-30 found a standard deviation of 11 giving a detectable effect size corresponding to 4.4 points [60]. Such a difference is considered plausible and of a magnitude worthwhile detecting if the intervention had such an effect.

The design of the intervention allows a rolling intake of participants in the various groups; therefore, there is potential for clustering in that arm (with no such effects in the control arm). The degree of this effect (essentially one of additional inefficiency/compromise on power) will depend on the degree of clustering, the number of intervention groups and the extent to which these groups overlap as men enter and leave them. All of these are difficult to predict; the latter in particular means that a clear definition of a cluster is very likely to be elusive. Hence, we have not allowed for this in the above power calculation but have explored the potential for such clustering effects using the clsampsi command in Stata 15.1 [61]. Notwithstanding these uncertainties, with a (conservative) intra-cluster correlation coefficient (ICC) of 0.05, the above sample size would yield a power of 80% to detect a 0.435SD effect size. The originally planned sample size would therefore have about 80% power to estimate an effect size of between 0.4 to 0.435 SD, covering situations with zero/negligible clustering and for a conservative ICC.

### Reduction in sample size

Due to difficulties experienced in meeting the original target for recruitment, primarily from the first 18 months of recruitment being conducted during the COVID-19 pandemic, along with an extended recruitment period, a reduction of 50 in this target was subsequently approved by the Programme Steering Committee (PSC), Data Monitoring and Ethics Committee (DMEC), and the funding body. Using the SD of 10.7 derived from 201 baseline measurements in this trial and again assuming 40% attrition, the revised sample size of 316 to be recruited provides approximately 80% power to detect an effect size of 0.43SD under the primary assumption of no clustering. This slightly revised target difference, corresponding to 4.6 ABI-29 scale points (compared with the original of 4.4), was still deemed plausible and worth detecting to drive implementation of the programme after the trial.

### Recruitment {15}

The study will be advertised through posters and leaflets in general practices, pharmacists and other local community settings including sports and exercise venues, pubs and church halls. Local social services, DVA forums and national DVA networks and helplines (for example, Respect) have been made aware of the study through newsletters and presentations and will be able to refer men to the study. A prospective participant can also self-refer into the study. A digital social media campaign providing targeted Facebook and Google adverts to males using specific search terms (such as *anger management*) and further social media campaigns will make use of Twitter, Instagram and Facebook to direct potential referrers, such as social services, to the study. Regular presentations and discussions will be held with these potential referrers to ensure they fully understand the rationale for the trial and the processes for men who are referred and for their (ex)partners.

## Assignment of interventions: allocation

### Sequence generation {16a}

Computer-generated sequence using a minimisation approach, stratified by centre. Each participant will be allocated to the group that would result in the smallest imbalance in the variable ‘partner status’ with probability of 0.8 to avoid the allocations becoming predictable.

### Concealment mechanism {16b}

Computer system accessed remotely by researcher. The male participant will be registered with the study before allocation is revealed.

### Implementation {16c}

The recruiting researcher accesses a website remotely, enters the required details and is immediately informed of the randomisation allocation. This is shared straightaway with the participant and the service provider.

## Assignment of interventions: blinding

### Who will be blinded? {17a}

Once participants are recruited and randomised, it is not possible to mask participants to their allocation. For the purposes of safety, it would not be appropriate to mask a participant’s (ex)partners, local intervention delivery team or local WSW to the participant’s allocation. Members of the research study team need to be unblinded to carry out research activities. However, all data entry and data quality checks will be performed by study administrative staff, masked to trial allocation.

### Procedure for unblinding if needed {17b}

Not applicable, given that it is not appropriate for the research team, intervention delivery teams, or male or female participants to the male participant allocation.

## Data collection and management

### Plans for assessment and collection of outcomes {18a}

Data will be collected at four timepoints: baseline, then 4, 8 and 12 months after recruitment. The primary method of data collection is by self-reported questionnaire. Participants will be asked to complete the questionnaires via an online survey (via a unique Research Electronic Data Capture (REDcap) weblink hosted by the university of Bristol) [62, 63], on paper in a face-to-face meeting, or by telephone with a researcher, according to preference or need.

Figure 2 sets out the details of the outcome measures being collected at which time points and the objectives of these measures.

Measures only collected at baseline are as follows: sociodemographic variables (age, ethnicity, sexuality, religion, education, employment, income, housing and number of children at home); current self-reported physical disability or mental health problems, including treatment; autism spectrum quotient (AQ-10) [50]; adverse childhood experiences (adapted from the PROVIDE survey [48] and juvenile victimisation questionnaire [41]) and the IMPACT monitoring toolkit (client or partner T0) [37].

### Plans to promote retention and complete follow-ups {18b}

The research team will endeavour to maintain contact and trial engagement with all participants every 6–8 weeks via text messaging (according to contact preference). Two to three weeks prior to a questionnaire’s due date, participants will be alerted by the method of their choice (text, email, or phone call) to the forthcoming questionnaire. Up to seven reminders may be sent via different means (calls, text, email) if the follow-up questionnaire has not been completed.

An eligible potential participant who chooses not to participate is counted as a *decline* and reasons for declining will be collected. Once consented, a participant may withdraw at any time should they wish. Participants allocated to the intervention who no longer wish to be involved in the programme will still be followed up with questionnaires. No further follow-up data will be requested from any individuals who explicitly wish to fully withdraw from the trial, but data collected up to that point will be retained and included for data analysis.

### Data management {19}

REDCap is a secure, web-based electronic data capture (EDC) system designed for the collection and management of research (as distinct from administrative) data. Although the REDCap system has been developed (and it is supported) by Vanderbilt University, Bristol Medical School has set up its own infrastructure to host the REDCap application so that all elements reside within UoB.

All questionnaire data are stored in a secured UoB server subject to standard UoB security procedures. Outcome data are anonymised by use of the ID number and no personal details will be held on the outcome database.

Both outcome (REDCap) and Administrative (AdminDB) data are secured using robust security mechanisms. Both systems also have audit logs cataloguing individual changes with data/time, old value, new value and the identity of the user who made the change.

### Confidentiality {27}

All personal information and research data can only be accessed by authorised accounts and authorisation can only be granted by specific people such as the chief investigator, the programme manager, or members of the research team.

Administrative data including names, addresses, contact details and other personalised data will be stored on a bespoke management database (AdminDB), designed and managed by the Bristol Trials Centre (BTC) and held in the University of Bristol (UoB) SQL Server Cluster. All participants will be allocated a unique numerical ID number which will be used to provide anonymity and track their data.

Where possible, personal identifiable details will be removed from hard-copy documents and replaced with the participant’s unique trial identification number. During the study, all hard-copy documents containing patient identifiable data will be stored separately from research data in (as a minimum) locked filing cabinets within alarmed, access-restricted University buildings of each of the research centres. Only local research teams will have access to these locked cabinets.

Electronic data will only be accessible via a password-protected database held on a secure server.

### Plans for collection, laboratory evaluation and storage of biological specimens for genetic or molecular analysis in this trial/future use {33}

N/A. No biological specimens will be collected in this study.

## Statistical methods

### Statistical methods for primary and secondary outcomes {20a}

Descriptive statistics will be used to summarise all baseline characteristics and outcome measures in both study arms.

The primary outcome of the ABI-29 will be analysed using a linear regression model that will include the baseline ABI-29 score, the stratification factor of centre and minimisation factor of relationship status. The primary analysis will be performed on a complete case basis and according to the arm to which the participant was allocated. Sensitivity analyses will be conducted to explore the effects of the number of sessions attended and (if possible, given the eventual structure of the intervention groups) any effects of clustering. Secondary outcomes will be analysed using linear or logistic regression models as appropriate. If found, substantial imbalances of variables at baseline (determined using descriptive statistics) will be explored in sensitivity analyses.

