### Trial design {8}

This is a multi-centre, two-group, pragmatic, individually randomised controlled trial with embedded process evaluation and economic evaluation. The bespoke online randomisation system is provided by the Bristol Trials Centre. Participants are randomly allocated in a 2:1 ratio to intervention or control respectively. Randomisation is stratified by centre (Bristol/North Somerset/South Gloucestershire (BNSSG), Somerset, Wiltshire, Blaenau Gwent and Neath Port Talbot) and minimised by relationship status (whether or not the participant is still living all or most of the time with the abused partner).

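### Under 2:1 allocation the usual pooled standard error for the primary linear regression is wrong, in either direction, if the arm variances differ; name a robust one (low severity)

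*Protocol article*

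**What the plan says.** Section {20a} of the protocol article states that the 12-month ABI-29 "will be analysed using a linear regression model that will include the baseline ABI-29 score", together with centre and relationship status, on complete cases as allocated. It does not say whether the standard error is model-based, robust or bootstrapped. The sensitivity analyses it lists deal with sessions attended, clustering and baseline imbalance, and section {20c} adds missing data. None deals with unequal variances.

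Section {8} fixes the allocation: "Participants are randomly allocated in a 2:1 ratio to intervention or control respectively". The section on the reduced sample size uses a single SD for both arms, taken before treatment: "Using the SD of 10.7 derived from 201 baseline measurements in this trial and again assuming 40% attrition". It concludes that "the revised sample size of 316 to be recruited" gives "approximately 80% power to detect an effect size of 0.43SD under the primary assumption of no clustering", which it equates to 4.6 points.

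Section {20b} says that a SAP will be agreed with the oversight committees before any comparison of the arms. That SAP is not shown.

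**The concern.** Least-squares regression in its default form estimates one residual variance from both arms together. With equal arms, a difference in variance between them hardly disturbs the standard error of the treatment effect. With 2:1 allocation it does. The pooled variance is weighted towards the larger intervention arm, while most of the sampling error comes from the smaller control arm. A gap between the two variances therefore passes into the standard error.

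The outcome makes such a gap plausible. ABI-29 is a 29-item inventory with a floor at no reported abuse. A programme that lowers abuse roughly in proportion would also shrink the spread in the larger arm, and the interval would then be too narrow. A programme that works for some men and not for others could widen the spread, and the interval would then be too wide.

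What is at stake is the stated precision of the effect on ABI-29, which the sample-size section links to the case for implementing the programme. The point estimate is not affected. The issue is also separate from correlation between men in the same group, which the article discusses elsewhere.

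**Working it through.** **Inputs from the protocol article.** Allocation 2:1; two-sided 5% level; 316 recruited; 40% attrition; SD 10.7; target 0.43 SD, or 4.6 points. Analysed: 316 × 0.6 = 189.6, so about 126 v 63.

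**Input assumed, not in the document.** r = 12-month SD in the intervention arm divided by that in the control arm, varied from 0.7 to 1.25. The control SD is set at 10.7.

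**Step 1: the plan's own figures, with equal SDs.**
- Revised design: 0.43/√(1/126 + 1/63) = 0.43/0.1543 = 2.787, so power = Φ(2.787 − 1.96) = 79.6%. The noncentral t gives 79.2%. The plan says about 80%.
- Original design, 146 v 73: 0.4/√(1/146 + 1/73) = 2.790, so power = 79.7%. The noncentral t gives 79.3%. The plan says 79%.

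The plan's figures reproduce. Both rest on equal SDs.

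**Step 2: pooled against true standard error, unadjusted comparison.**
- Pooled SE = √{[(125 s₁² + 62 s₂²)/187] × (1/126 + 1/63)}
- True SE = √(s₁²/126 + s₂²/63)
- Their ratio is close to √[(2r² + 1)/(r² + 2)]
- Coverage ≈ 2Φ(1.96 × ratio) − 1

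Example at r = 0.8, in units of the control SD: pooled SE = √(142/187) × 0.1543 = 0.1345; true SE = √(0.64/126 + 1/63) = 0.1447; ratio 0.929.

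| r | Pooled SE (points) | True SE (points) | Ratio | Coverage of 95% CI |
|---|---|---|---|---|
| 0.7 | 1.340 | 1.504 | 0.891 | 91.9% |
| 0.8 | 1.439 | 1.549 | 0.929 | 93.1% |
| 0.9 | 1.543 | 1.598 | 0.965 | 94.1% |
| 1.0 | 1.651 | 1.651 | 1.000 | 95.0% |
| 1.1 | 1.763 | 1.708 | 1.032 | 95.7% |
| 1.25 | 1.937 | 1.799 | 1.076 | 96.5% |

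With the same total split 1:1, the ratio is 1.00 at r = 0.7, 0.8 and 1.2.

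**Step 3: check in the baseline-adjusted model by simulation.** 126 v 63, 4,000 runs per scenario. Assumed: gamma-shaped scores with SD 10.7, baseline to follow-up correlation 0.6, mean above the floor 20 unless stated, average effect 4.6 points except under no effect.

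| Scenario | SD ratio | Usual SE (mean) | Empirical SD | Coverage, usual | Coverage, HC3 |
|---|---|---|---|---|---|
| No effect in any man | 1.02 | 1.319 | 1.319 | 94.9% | 95.1% |
| Uniform shift | 1.02 | 1.318 | 1.303 | 95.8% | 96.0% |
| Proportional fall, mean 15 | 0.71 | 1.073 | 1.214 | 91.4% | 94.6% |
| Proportional fall, mean 20 | 0.79 | 1.130 | 1.242 | 92.4% | 94.7% |
| Proportional fall, mean 30 | 0.86 | 1.192 | 1.273 | 93.7% | 95.0% |
| Half the men fall by 9.2 points | 1.11 | 1.440 | 1.390 | 95.7% | 95.4% |

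A second simulation of the proportional fall (correlation 0.5, mean above the floor 12 to 25) gave 90.9% to 93.0% with the usual SE and 94.5% to 95.0% with HC3. When only 50% to 60% of men respond, each by a proportional fall and with the same average effect, coverage with the usual SE was about 93% to 95%.

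**Step 4: price of HC3 when it is not needed.** With no effect, the mean SE rises from 1.319 to 1.331, or 0.9%. With a uniform shift it rises from 1.318 to 1.332, or 1.1%.

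**The case against.** The strongest reply is that section {20a} commits to a linear regression and not to any standard error. HC3 is compatible with every word of it. The choice of variance estimator is ordinary SAP content, and the SAP is not shown. This stands: silence on the estimator is not an error in the article, and it would be wrong to say that the plan has adopted the pooled standard error. What remains is narrower. The article fixes an allocation under which the software default is fragile, and a better choice costs almost nothing.

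A reader might go further and infer that the interval is too narrow whenever the programme works. The document does not support this. It gives only baseline SDs. A uniform shift of 4.6 points leaves the interval correct, and a split into responders and non-responders can make it slightly too wide. Partial response is also realistic here: the article provides for men being removed from the programme while still followed up, and for analyses by sessions attended and by compliance. The lowest coverage found, 90.9%, needs every man to respond in proportion and the lowest assumed mean above the floor.

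A reader might also fear extra false positives from an inert programme. If no man is affected, the variances are equal and the test stays at about 5%.

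**Conclusion.** The point holds in conditional form and at low severity. If the usual pooled standard error is used with about 126 v 63 men, it is mis-stated whenever the arm variances differ. It is 3.5% to 11% too small for SD ratios of 0.9 down to 0.7, with coverage of about 94% down to 92%. It is 3% to 8% too large for ratios of 1.1 to 1.25. It is correct at a ratio of 1. The mechanism follows from the 2:1 allocation. The direction and size rest on an assumed ratio of 12-month SDs, and the simulations also assume the score shape, the mean above the floor and the baseline correlation. Compression towards the floor is plausible but not established. The plan's power figures are sound under their equal-SD assumption, and nothing in the article is contradictory on this point.

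**What to change.** State in section {20a} or the SAP, before any comparative analysis, that the primary model and the other linear models report heteroscedasticity-consistent (HC3) standard errors, with confidence intervals and p-values based on them. The covariates, analysis population and point estimate do not change. The cost is one line of text and one software option, plus intervals about 1% wider if the variances turn out equal. If the SAP already names a robust or bootstrap standard error, nothing more is needed.
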